### 3.3 MANAGING POTENTIAL RISKS

*Describe what measures you have in place to minimize these potential risks to participants and to ensure that support is available if needed.* [Depending on risks, participants may need additional support (e.g. external counseling) during or after the study]

Some potential participants may screen positive for major depression. The screening questionnaire is a brief self-report measure that cannot give a diagnosis on its own, but can indicate whether a diagnosis is probable. In this instance, participation in the project may not be the most appropriate strategy to improving mental health. These participants will not be eligible for participation; rather, they will be informed that they may have major depression and should seek appropriate professional help. Appropriate sources of help will be provided on the website (see Appendix F).

### 3.4 DEBRIEFING (if applicable)

*What debriefing will participants receive following the study and when? (Attach a copy of any written material or statement to be used in such a debriefing, if applicable).* [Participants may need to talk about the experience of being involved in the study with the researchers, as well as learn more about the aims of the research]

Not applicable.

### 3.5 BENEFITS COMPARED TO POTENTIAL RISKS

*Outline the benefits of the study to the community (and participants, if applicable), relative to the potential risks to participants*

As participation is limited to those who are not being treated for their depression, participation may benefit the participants through improving their depression symptoms and mental wellbeing. The study may also benefit the community through adding to knowledge about ways to reduce or prevent depression, knowledge which can be promoted to the community as a whole. As the intervention involves benign strategies thought to be helpful by experts, and participants can withdraw if their symptoms worsen, the benefits outweigh the potential risks. Even if the results are non-significant, the study is adequately powered to be able to rule out the potential effectiveness of this approach. This will benefit the community by protecting them against the mounting of public health campaigns with no evidence base.

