### 1. PROJECT DETAILS

- 1.1 EXECUTIVE SUMMARY IN PLAIN ENGLISH:** *Provide a brief summary of the project outlining the broad aims, background, key questions, research design/approach, the participants in the study and what they will be asked to do, and the importance or relevance of the project. [This description must be in everyday language, free from jargon, technical terms or discipline-specific phrases. (No more than 300 words).]*

People who are not clinically depressed, often have some depressive symptoms. These symptoms impair the person's functioning and may develop into major depression. Self-help strategies, such as exercise or taking time off work, are acceptable and often used by those with depressive symptoms. However, some strategies are not as effective as others, and some may be harmful (e.g. substance use). Previous research has identified a set of self-help strategies thought to be helpful by an international group of depression experts. This project will test the effectiveness and feasibility of promoting these helpful self-help strategies to individuals with depressive symptoms (but not major depression) in a randomised controlled trial. The internet will be used to recruit participants, assess outcomes and deliver the intervention, which will consist of email messages based on the self-help strategies. The effect of these will be compared to receiving emails containing general information about depression. A variety of outcomes will be assessed, including effects on symptoms, general wellbeing, and social and occupational functioning. The aims are twofold: (1) to assess the feasibility of conducting a health promotion campaign of self-help messages for individuals with some depression symptoms, and the viability of using the internet for the campaign; and (2) to reduce the overall level of depressive symptoms as well as the number of individuals developing major depression.

- 1.2 AIMS OF AND JUSTIFICATION FOR THE RESEARCH:** *State the aims and significance of the project. Where relevant, state the specific hypothesis to be tested. Also provide a brief description of current research/literature review, a justification as to why this research should proceed and an explanation of any expected benefits to the community. [No more than 500 words]*

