Participants will be recruited to the project website (<http://www.moodmemos.com>) by advertising on Google, links from depression and mental health websites and blogs, and posts on mental health forums. See Appendix A for a letter proforma asking whether webmasters would like to put a link to the moodmemos.com website on their website. An online screening questionnaire (Patient Health Questionnaire-PHQ9; Kroenke & Spitzer, 2002) will assess level of depressive symptoms and probable diagnosis of major depressive disorder. Participants who have sub-threshold depression symptoms will be provided with a plain language statement and invited to participate. They will be asked to complete a number of online questionnaires assessing psychological distress (K10; Kessler et al., 2002), functioning (Work and Social Adjustment Scale; Mundt et al., 2002) unpleasant experiences that may have caused depression (List of Threatening Experiences; Brugha et al., 1985), coping strategies, knowledge about depression, and sociodemographics (see Appendix B for all questionnaires), and to provide a name and email address. Those who meet admission criteria will be randomised to receive the active intervention or a control of educational information about depression. The intervention will be run on the internet and will be automated as much as possible through php computer scripts. The active group will receive email messages based on strategies thought to be effective and feasible by depression experts (Morgan & Jorm, 2009). See Appendix C for the text of each active message and an example of the layout of the email.

The control group will receive email messages based on information about depressive disorders, such as prevalence and risk factors. See Appendix D for the text of each control message and an example of the layout. The intervention will run for 6 weeks with emails sent twice a week. In addition to baseline, assessments will take place midway through the intervention, at the end of the intervention and 6 months after the end of the intervention. Total time commitment is estimated to be no more than 3 hours, including time to read each email as well as time taken to complete the four assessments.

Continuous outcomes (e.g. depressive symptoms) will be evaluated using mixed effects regression models, and dichotomous outcomes (e.g. presence of a depressive disorder) will be evaluated using logistic regression expressed as odds ratios with their 95% confidence intervals.

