**2.2 NUMBER, AGE RANGE AND SOURCE OF PARTICIPANTS**

*Provide number, age range and source of participants.*

We will aim for a minimum of 1200 participants aged 18 or over from the following countries: Australia, New Zealand, UK, Ireland, Canada and USA. These countries were chosen because the research investigating appropriate self-help strategies was limited to these English-speaking countries.

**2.3 JUSTIFICATION OF PARTICIPANT NUMBERS** [The quality and validity of research is an essential condition of its ethical acceptability (refer National Statement)]. *Where applicable, provide a justification of sample size (including details of statistical power of the sample, where appropriate), explaining how this sample size will allow the aims of the study to be achieved.*

According to Cohen (1992), a sample of 393 per condition gives 80% power to detect a small effect size (0.2 standard deviations between conditions). Because depression Internet trials have a median dropout rate of 33% (Christensen et al., 2009), a total sample of 1200 participants will be aimed for.

Cohen, J. (1992). A power primer. *Psychological Bulletin* 112: 155-159.  

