We will continue to advertise the study and recruit participants in the same manner as before (primarily through Google advertising). We will aim for a sample size of 1600 participants in this second phase of the study. This is based on a power analysis indicating that a sample of 393 per condition would give 80% power to detect a small effect size (0.2 standard deviations between conditions) on a continuous outcome measure assuming a correlation of 0.5 between pre- and post-test scores. As approximately 50% of participants in phase one did not complete the post-test assessment, a total sample of 1600 allows for a similar rate of attrition. 1600 participants is a feasible target given that 1336 participants with sub-threshold depression were recruited in phase one.

To clarify, the inclusion criteria will now be:

- a. 18 years or older
- b. Access to the internet at least once per week
- c. Resident of Australia, New Zealand, Canada, Ireland, United Kingdom, USA
- d. Any score on the PHQ-9 depression questionnaire
- e. Informed consent

2) The second change we propose is to send an additional reminder email requesting the participant to complete post- and follow-up assessments, bringing the number of reminders to two. This is because up to 50% of participants did not complete assessments, and the reminder email resulted in about 25% more responses. Therefore, a second reminder may lead to a significantly higher response rate.

3) The third change we propose is to amend the wording of the help-seeking question asked at mid-point, post intervention and follow-up. This is so that we can collect more specific information about treatments received by participants. The question will be changed from:

"Have you visited a health professional (e.g. doctor, counsellor, psychologist) to help deal with your depression during the past [3 weeks] / [6 weeks] / [6 months]? (Yes/No)"

to:

"Which treatments for depression have you received from a professional during the past [3 weeks] / [6 weeks] / [6 months]? (multiple responses allowed)

• Nothing, just the consultation

• Psychological therapy

o Acceptance and commitment therapy

o Behaviour therapy

o Cognitive behaviour therapy

o Dialectical behaviour therapy

o Family therapy

o Mindfulness-based cognitive therapy

o Problem solving therapy

o Psychoanalytic psychotherapy

o Supportive psychotherapy or supportive counselling

o Not sure what type

• Medication

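### Section 3.5 says a non-significant result would rule out effectiveness; 80% power at 0.2 SD does not support that, and nothing was sized for major depression

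*Protocol*

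**What the plan says.** Section 3.5 of the protocol, weighing benefits against risks, states: "Even if the results are non-significant, the study is adequately powered to be able to rule out the potential effectiveness of this approach". It adds that the community gains because campaigns lacking evidence would then not be launched.

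The sizing is in section 2.3: "a sample of 393 per condition gives 80% power to detect a small effect size (0.2 standard deviations between conditions". After allowing for dropout, "a total sample of 1200 participants will be aimed for". The amendment (section 4.1) uses the same 393 per condition, 80% and 0.2 SD for phase two, specified there for a continuous outcome. It does not revisit section 3.5.

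Section 1.1 gives the effectiveness aim as "to reduce the overall level of depressive symptoms as well as the number of individuals developing major depression". Section 1.3 analyses continuous outcomes by mixed-effects regression and dichotomous ones by "logistic regression expressed as odds ratios with their 95% confidence intervals". No event rate, target effect or power is given for a dichotomous outcome. The document states no margin or smallest worthwhile effect, and no rule for reading a null result from its interval.

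**The concern.** The sentence makes non-significance the trigger for concluding that the approach does not work. Power of 80% at 0.2 SD describes how often a real effect of that size would be detected. It does not mean that failing to detect an effect excludes one. What can be excluded depends on where the confidence interval lies.

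At stake is how a null trial is read. Taken at its word, section 3.5 would let an inconclusive result be reported as evidence of ineffectiveness and used against later public-health work. The claim also covers the approach as a whole, so it takes in prevention of major depression, for which the protocol offers no sizing.

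**Working it through.** **Inputs**
- 393 per arm, 80% power, 0.2 SD: protocol section 2.3.
- Two-sided 5% test: not stated. Inferred because it reproduces 393 (a one-sided 5% test gives 310) and fits the 95% intervals in section 1.3.
- Equal allocation: inferred from the per-condition figure.
- Effects are in SD units, and positive values favour the active emails.

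**1. Reproduce the plan's figure.** n = 2(1.960 + 0.8416)² / 0.2² = 2 × 7.849 / 0.04 = 392.4, so 393 per arm. With 33% dropout, 786 / 0.67 gives 1174. The stated 1200 leaves 1200 × 0.67 / 2 = 402 per arm. The sizing arithmetic is sound.

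**2. Precision at 393 per arm.** SE = √(2/393) = 0.0713. The 95% half-width is 1.96 × 0.0713 = 0.140.

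**3. Chance of missing the design effect.** Power = Φ(0.2/0.0713 − 1.96) = Φ(0.84) = 0.80, so a true 0.2 SD effect is non-significant 20% of the time.

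**4. Highest upper limit of a non-significant result.** The estimate can be just under 0.140, so the upper limit can reach 0.140 + 0.140 = 0.28 SD.

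**5. Estimate needed to exclude 0.2 SD.** It must be below 0.2 − 0.140 = 0.060 SD. Estimates from 0.060 to 0.140 are non-significant but leave 0.2 SD inside the interval.

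**6. How often each happens.** For true effect δ, P(interval lies below 0.2) = Φ((0.0602 − δ)/0.0713).

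| True effect (SD) | Non-significant | Interval lies below 0.2 SD | Share of non-significant results that exclude 0.2 SD |
|---|---|---|---|
| 0 | 95% | 80% | 82% |
| 0.10 | 71% | 29% | 40% |
| 0.20 | 20% | 2.5% | 13% |

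The last row shows the cost of the current wording. With a true effect of 0.2 SD, calling every non-significant result a rule-out is wrong 20% of the time; requiring the interval to exclude 0.2 SD is wrong 2.5% of the time. In the middle row, the probability of being non-significant without excluding 0.2 SD is 0.423, and 0.423 / 0.711 = 60% of non-significant results.

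**7. Does another sample size or analysis rescue the sentence?** The highest upper limit of a non-significant result is twice the half-width. Baseline adjustment multiplies the half-width by √(1 − r²) = √0.75 at the amendment's r = 0.5.
- 402 per arm (1200 at 33% loss): 2 × 0.138 = 0.28.
- 400 per arm (phase two, 1600 at 50% loss): 2 × 0.139 = 0.28.
- 393 per arm, adjusted: 2 × 0.121 = 0.24.
- 334 per arm (phase one, 1336 × 0.5 / 2): 2 × 0.152 = 0.30 unadjusted, 2 × 0.131 = 0.26 adjusted.

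All exceed 0.2 SD.

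**8. Major depression.** The aim is in section 1.1 and the method in section 1.3, but neither section 2.3 nor the amendment sizes it. As illustration only, with assumed control risks of 5%, 10%, 15% and 20% and 402 per arm, power for a 25% relative reduction is 14%, 24%, 35% and 46%. For a halving it is 46%, 77%, 92% and 98%. The answer depends on inputs that the protocol does not give.

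**The case against.** **It is one sentence in an ethics form, not an analysis rule.** This is fair as to its reach. Section 1.3 contains no rule that p > 0.05 means no effect, and no model, sample size or eligibility criterion depends on section 3.5. A reader might infer that the analysis itself is built on such a rule; the document does not say so. Still, the sentence asserts a property that the design lacks, and nothing elsewhere corrects it.

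**The design does have some capacity to rule out its target effect.** This stands. If the true effect is zero, there is about an 80% chance that the interval excludes 0.2 SD. That capacity comes from the position of the interval, however, and it falls to 29% at a true effect of 0.1 SD.

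**Attrition.** The amendment reports: "As approximately 50% of participants in phase one did not complete the post-test assessment". A reader might infer that this is what makes section 3.5 wrong, or that phase one had only 73% power. Neither follows. The figure became known only after section 3.5 was written, and phase two is sized for it (400 per arm, about 81% power). The 73% belongs to an unadjusted comparison of 334 completers per arm; baseline adjustment at r = 0.5 gives about 85%, and the planned mixed model may also use partial data. Attrition is context, not an error in section 3.5.

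**Power for major depression.** A reader might infer that the trial is shown to be underpowered for this aim. The documents give neither an event rate nor a target effect, so that cannot be established. What can be said is that no sizing is stated.

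**Conclusion.** The sentence in section 3.5 is wrong as written. With the protocol's own 393 per arm, a non-significant result is compatible with benefits up to about 0.28 SD, and a true 0.2 SD effect would be missed one time in five. Ruling out 0.2 SD needs an estimate below about 0.06 SD, with a probability of about 80% at a true effect of zero and 29% at 0.1 SD. No rule-out claim is supported for major depression, because nothing was sized for it.

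The figures assume a two-sided 5% test, equal allocation and an unadjusted comparison. Adjustment narrows the interval but does not change the conclusion. The value 0.2 SD is used because it is the effect the study was sized to detect; the protocol does not call it the smallest worthwhile effect. The sample-size calculation itself is correct.

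**What to change.** Replace the sentence in section 3.5 with:

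> A null result will be interpreted from the 95% confidence interval. On depressive symptoms, a benefit of 0.2 SD (the effect the study was sized to detect) will be regarded as ruled out only if the interval excludes it; otherwise the result is inconclusive. No rule-out claim is made for major depression, for which the study was not sized.

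The sentence that follows, on the benefit of a null result to the community, should be made conditional in the same way. Nothing else has to change: the sample size, the models, the standing of major depression as an aim and the stated power for either phase can stay as they are.

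The cost is wording only. The downside is that the community benefit claimed for a null result, which forms part of the case put to the ethics committee, becomes less favourable.

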### 3.6 MANAGING ADVERSE / UNEXPECTED OUTCOMES

*Describe what measures you have in place in the event that participants experience adverse effects arising from their involvement in the project (e.g. adverse drug reaction, revelation of illegal activity, or unexpected distress due to questioning)*

Despite the intervention, some participants may develop major depression or become acutely suicidal. To manage this risk, participants will be encouraged throughout the project to seek help from a professional if they feel they are getting worse. To facilitate this, a section of the website will provide information on seeking professional help for each country involved. Participants will also receive feedback from their survey results on their level of symptoms, and encouraged to seek professional help if their symptom levels indicate major depression. Currently many people with depression do not seek and/or receive help for their symptoms. The links provided on the website will channel potential participants using the Internet for mental health information to appropriate sources of help. Participants will be informed they can discontinue participation at any time.

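### Section 3.5 reads a non-significant result as ruling out the approach and protecting against baseless campaigns, but the trial estimates only the added benefit over depression-information emails, and non-significance alone does not exclude the planned 0.2 SD

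*Protocol*

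**What the plan says.** Section 3.5, which weighs benefits against risks, makes two linked statements about a null result. The first concerns inference: "Even if the results are non-significant, the study is adequately powered to be able to rule out the potential effectiveness of this approach". The second concerns public benefit: "This will benefit the community by protecting them against the mounting of public health campaigns with no evidence base".

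The comparison is defined elsewhere. Section 1.1 says of the self-help emails: "The effect of these will be compared to receiving emails containing general information about depression". Section 1.3 describes the active arm ("The active group will receive email messages based on strategies thought to be effective and feasible by depression experts") and the control arm ("The control group will receive email messages based on information about depressive disorders, such as prevalence and risk factors"). On timing it says: "The intervention will run for 6 weeks with emails sent twice a week". No arm goes without emails.

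Section 3.6 describes support given to participants in general, with no mention of arm: "Participants will also receive feedback from their survey results on their level of symptoms", and "participants will be encouraged throughout the project to seek help from a professional if they feel they are getting worse". It also places help-seeking information for each country on the website.

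Section 2.3 gives the sample size: 393 per condition for 80% power at a difference of 0.2 SD between conditions, raised to 1200 in total for 33% dropout.

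**The concern.** A decision about mounting a public health campaign is most naturally a choice between running it and not running it. The trial does not make that comparison. It compares two email series on depression, with feedback and help-seeking advice common to participants. A difference near zero is what would be seen if neither series helped, and also if both helped equally. The data cannot tell these apart.

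The preceding sentence has a further fault. It treats non-significance, in a trial with 80% power, as enough to rule out effectiveness. What a null result excludes depends on the confidence interval, not on the planned power.

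At stake is what may be concluded from a null. As worded, section 3.5 would let a non-significant symptom result be presented as evidence against self-help campaigns in general. It also offers the ethics committee a benefit that the design does not deliver in that form. The same limit applies to a positive result, which would be a gain over information emails and not the effect of running a campaign.

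**Working it through.** **1. The contrast.** Write A for the mean benefit of the self-help emails and C for that of the information emails, each in SD units and each against receiving no emails, with feedback and help-seeking advice present throughout. The trial estimates A − C. Section 3.5, on its campaign reading, needs A, or A plus the effect of the shared feedback and advice. Neither can be recovered from A − C unless C is known, and the documents give no value for C.

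**2. The plan's own figure.** Inputs from section 2.3: difference 0.2 SD, power 80%. Two-sided 5% and 1:1 allocation are not stated and are assumed here.
- n per arm = 2 × (1.960 + 0.842)² / 0.2² = 392.5, so 393. The stated figure reproduces.
- 2 × 393 = 786; 786 / (1 − 0.33) = 1173.1, so 1174, which the plan rounds up to 1200. No sample-size figure is wrong.

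**3. What non-significance excludes at 393 per arm, unadjusted.**
- Standard error = √(2/393) = 0.0713 SD.
- 95% half-width = 1.96 × 0.0713 = 0.140 SD.
- A result just short of significance has an observed difference of about 0.14, so its upper limit is 0.14 + 0.14 = 0.28 SD.
- The upper limit falls below 0.2 only if the observed difference is below 0.20 − 0.14 = 0.06 SD. Observed differences from 0.06 to 0.14 SD are non-significant yet do not exclude the planned effect.
- If the true difference is zero, the chance that the upper limit falls below 0.2 is Φ(0.2/0.0713 − 1.96) = 80%.

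**4. Sensitivity.**
- Baseline adjustment with r = 0.5, the correlation that section 4.1 of the amendment request assumes for phase two: half-width 0.140 × √(1 − 0.25) = 0.121, so the largest non-significant upper limit is 0.24 SD.
- Phase one as the amendment describes it (1336 recruited, about 50% without a post-test): about 334 per arm if equally split. The half-width is 0.152, the largest upper limit 0.30 SD, and power for 0.2 SD is 73%, all unadjusted.

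**5. Possible dilution, as illustration only.** Suppose A = 0.20 SD and let C vary. C is an assumption.

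| Assumed C | A − C | Chance of significance, 393 per arm | Same, 10,000 per arm |
|---|---|---|---|
| 0 | 0.20 | 80% | 100% |
| 0.05 | 0.15 | 56% | 100% |
| 0.10 | 0.10 | 29% | 100% |
| 0.15 | 0.05 | 11% | 94% |
| 0.20 | 0 | 2.5% in favour of self-help | 2.5% in favour of self-help |

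The middle rows describe low power, which a larger trial cures. Only the last row shows a shared effect that no sample size recovers.

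**The case against.** The best defence is that the approach in section 3.5 means promoting these particular self-help strategies. On that reading an information-email control is a legitimate attention control, and a precise null against it does bear on whether to promote the strategies. Section 3.1 of the form ticks the item for non-treatment or placebo controls, so the plan treats the control as close to inert. No passage shows that facts about prevalence and risk factors, or symptom feedback, reduce symptoms. Feedback and help links are also ordinary safety measures.

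Much of this stands. The control is a defensible choice, and dilution is possible but not demonstrated. The defence does not rescue the wording, however. Sections 1.2 and 3.5 speak of health promotion and public health campaigns, so the campaign reading is the more natural one. Even the narrow reading needs the qualifier that any benefit is measured over information emails, and section 3.5 omits it. The step from non-significance to ruling out fails on either reading.

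A reader might also infer that no sample size could make the comparison informative. That holds only if the conclusion means campaign versus no campaign. Or a reader might infer that a campaign worth 0.20 SD would be missed 44% to 89% of the time. Those figures are the complements of 56% and 11% in the table. They rest on assumed control effects, leave out zero, and largely disappear at a larger sample size.

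Finally, the count of 12 emails is 6 × 2. The schedule is not stated separately for controls, so nothing here depends on it.

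**Conclusion.** The concern holds in limited form. Section 3.5 overstates what a null result would show, in two respects.

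- **Scope.** The trial estimates the benefit of self-help content over general depression information, with feedback and help-seeking advice not restricted by arm. A null does not show that a self-help email campaign has no effect compared with no campaign. This follows from the design and needs no assumption about the control's effect. How far the two contrasts differ is unknown, and the difference may be zero.
- **Strength.** At 393 per arm a non-significant result can be compatible with a benefit of up to about 0.28 SD (0.24 with baseline adjustment at r = 0.5, 0.30 unadjusted at 334 per arm). Non-significance alone therefore does not exclude the planned 0.2 SD, even against the control actually used. These limits assume a two-sided 95% interval and equal arms.

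A reader might go further and conclude that the control is mislabelled or that aim 2 is unsound. The documents do not support that. Section 1.3 already calls the control educational information, and aim 2 states a goal without drawing anything from a null. The fault lies in a benefit statement. It does not touch the arms, the analysis or the sample size.

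**What to change.** Replace the two sentences in section 3.5 with wording such as:

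> If the 95% confidence interval for the difference between arms excludes a benefit of 0.2 SD, the study will show that self-help emails add little beyond general depression-information emails when both groups receive symptom feedback and help-seeking advice. It will not show how either email series compares with no emails.

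Delete the sentence about protecting the community from campaigns, or qualify it in the same terms.

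The cost is a change of wording and a narrower stated benefit.
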